## Methods

### Study Design

This study is a randomized trial with 2 parallel arms and a blinded evaluation. The study will be conducted at a university hospital that offers specialized treatment for moderate to severe asthma. The study protocol was developed in accordance with the SPIRIT (Standard Protocol Items: Recommendations for Interventional Trials) checklist guidelines [15], and the trial is registered at ClinicalTrials.gov (NCT05364632). The study flow diagram is presented in Figure 1.

After a regular medical visit, adult outpatients with asthma will be invited to participate in the study, and asthma pharmacotherapy will be maintained during the intervention. Initially, eligible patients will be randomized by a researcher not involved in the study using a computer-generated sequence into 2 groups: the AT group or the BI group. The total duration of each intervention for both groups will be 12 hours (720 minutes). Both groups will be evaluated before and after the interventions and again 16 weeks later. The evaluations will be carried out in a blinded fashion by an evaluator who will not be directly involved in the interventions.

**Figure 1 figure1:**
[figure not shown]
Study flow diagram of participant recruitment, randomization, interventions, and follow-up assessments. PADL: physical activity in daily life.

### Participants

The study will include adults of both sexes aged 18 to 65 years with moderate to severe asthma [16] who are physically inactive (less than 150 minutes of moderate to vigorous physical activity per week) [17], and patients with uncontrolled asthma (Asthma Control Questionnaire [ACQ]≥1.5) [18]. In addition, the following inclusion criteria will be considered: diagnosis of asthma based on Global Initiative for Asthma recommendations [1], outpatient medical treatment for at least 6 months, and a stable clinical status for at least 30 days (no hospitalizations, visits to emergency services, or medication changes) [19].

### Ethical Considerations

Patients will be recruited from the pulmonology outpatient clinic of the Hospital das Clínicas de São Paulo, São Paulo, Brazil. This study will be conducted in accordance with the Declaration of Helsinki. The hospital research ethics committee approved the study (51929221.7.0000.0068). All participants will be informed about the possibility of withdrawing at any time without incurring any loss of treatment at the institution. Participants will receive an identification code upon inclusion in the study. The data will be deidentified by excluding the main identifying elements such as name, address, date of birth, phone number, email, medical record number, institutional identification number, and social security number. In addition, patients will be informed about the voluntary nature of their participation. Financial assistance for transportation will be available. Informed consent will be obtained by researchers from all study participants.

### Randomization

The randomization sequence will be computer-generated via an online platform (Sealed Envelope [20]) and implemented by an independent researcher who will be unaware of the sequence. The researcher will not be involved in recruitment, assessment, or treatment. As described previously, the randomization sequence will be concealed using opaque sequentially numbered envelopes [21]. Each envelope will correspond to one of the 2 study groups, and participants will be sequentially assigned to the envelopes after the initial assessments.

### Analysis of the Population

The exclusion criteria will include participation in another study, current smokers or ex-smokers (who stopped smoking less than 1 year ago or had a smoking history of more than 15 pack-years), other associated lung or heart diseases, a diagnosis of cancer in the last 5 years, difficulty understanding any questionnaires, pregnancy, or psychiatric problems that prevent an understanding of the questionnaires. If a patient misses any session, the session will be rescheduled. Attending at least 75% of sessions will be considered the cutoff point to establish patient compliance for both groups [22-24]. An intention-to-treat analysis will be performed using the patient’s most recent assessment in case of withdrawal from the study or absence of data [25].

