**Objectives**

As previously mentioned, evidence suggests that AT or BI can improve asthma symptoms and reduce comorbidities. However, the comparison between these interventions in improving asthma control remains poorly understood. We hypothesize that these interventions will promote similar benefits in asthma control and quality of life in people with asthma. The main objective of this study is to compare the effects of AT versus BI in increasing physical activity for clinical asthma control. The secondary outcomes will include quality of life, physical activity level, sleep quality, asthma exacerbations, behavioral stages of physical activity, body composition, anthropometric variables, anxiety and depression symptoms, and cardiopulmonary exercise testing (CPET).

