### Statistical Analysis Planning

The sample size calculation (n) was established based on the clinical control measured by the ACQ to detect a clinical improvement of 0.5±0.6 points [34]. The required sample size will be 24 patients per group for a total of 48 patients, and a 15% loss will be considered, resulting in a total of 56 patients. The sample power was considered 80% with a significance level of 5%. Before the interventions, clinical, anthropometric, physical fitness, PADL, and psychosocial data obtained at baseline will be compared using the 2-tailed *t* test or Mann-Whitney test (depending on data normality) for continuous variables. The chi-square test will be used to compare categorical variables. After the intervention, time and group interactions will be evaluated using a two-way repeated measures ANOVA. The significance level will be adjusted at *P*<.05 for all tests, and the SigmaStat (version 3.5; Systat Software) program will be used for statistical analysis. All the analyses will follow the intention-to-treat principles until 15% of the data are missing. For confidentiality, the participants will be given an anonymous study ID, and only the study investigators will have access to the final trial dataset.

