### Strengths and Limitations of the Study

This study protocol will be a randomized trial with a 4-month follow-up postintervention. It is essential to determine whether the possible gains will be maintained in the medium term following the intervention. Objective measures of physical activity and sleep quality (ActiGraph GT9X), physical fitness (CPET), and body composition (Octopolar InBody 720) are another strength of this study. One limitation is that assessments using questionnaires are considered subjective measures. However, all tools have been validated and are widely used in interventions for people with asthma. The fact that the study will be conducted in a single hospital center may represent another limitation.

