### Conclusions

To the best of our knowledge, this will be the first study to compare the effects of AT versus BI on increasing physical activity for clinical asthma control. Therefore, the results obtained in the proposed protocol may provide essential information for health care professionals when recommending these approaches to people with asthma. Additionally, this study may help clarify whether the potential short-term gains following the intervention are maintained in the medium term in people with moderate to severe asthma.

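### Carrying the last assessment forward gives early dropouts zero ACQ change and later dropouts zero relapse, which biases both the arm comparison and the maintenance question

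*Protocol article*

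**What the plan says.** Under Analysis of the Population, the article states an intention-to-treat analysis that uses the patient's "most recent assessment in case of withdrawal from the study or absence of data". Statistical Analysis Planning adds one limit: "All the analyses will follow the intention-to-treat principles until 15% of the data are missing". The article describes no other missing-data method and no sensitivity analysis.

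On timing, Study Design states: "Both groups will be evaluated before and after the interventions and again 16 weeks later". Table 2 schedules asthma control at enrollment, at 8 weeks and at follow-up, with nothing in between. The analysis is that "time and group interactions will be evaluated using a two-way repeated measures ANOVA".

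Two stated aims bear on the rule. Objectives gives the hypothesis: "We hypothesize that these interventions will promote similar benefits in asthma control and quality of life in people with asthma". Strengths and Limitations says of the follow-up: "It is essential to determine whether the possible gains will be maintained in the medium term following the intervention". The Conclusions repeat that "this study may help clarify whether the potential short-term gains following the intervention are maintained in the medium term".

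**The concern.** LOCF is chosen explicitly here, so this is not a detail left to an unseen analysis plan. With only three ACQ measurements, its effect on each patient with missing data is fixed in advance:

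- **Lost before week 8:** the enrollment ACQ is carried forward, so the change is exactly 0, whatever happened to the patient.
- **Lost after week 8:** the week-8 ACQ is copied into the follow-up visit, so the loss of benefit is exactly 0.

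The first affects the comparison of the arms. If dropout is equal, a real difference is pulled towards zero, which is the direction of the hypothesised similarity. If dropout is unequal, a false difference can appear. Unequal dropout is possible, since one arm attends 16 treadmill sessions and the other 8 individual counselling sessions.

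The second affects the maintenance question. For patients missing at follow-up, the rule assumes the answer that the visit is meant to supply.

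**Working it through.** **Inputs from the article.** The planning statement is "to detect a clinical improvement of 0.5±0.6 points", with 80% power, 5% significance, 24 per group, 48 in total, 15% loss and 56 enrolled (Statistical Analysis Planning). That gives 28 per arm. A change of 0.5 ACQ points is clinically significant (Primary Outcome).

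**Assumptions.** The test is two-sided. The 0.6 is taken as the SD of the change score. True gains and dropout splits are varied. Dropout is completely at random, so dropouts would have gained as much as completers. The test is a two-sample t test on change from baseline.

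**The plan's own figure.** For a difference of 0.5 and SD 0.6, the t-test calculation gives 23.6, so 24 per arm (power 80.7%). Then 48 × 1.15 = 55.2, so 56. The stated figures reproduce, and this point does not alter them.

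**Week 8, equal dropout d.** The expected LOCF difference is (1 − d) × true difference = 0.85 × 0.5 = 0.425. The variance of the LOCF change in an arm with gain g is (1 − d)·SD² + d(1 − d)·g². For gains 1.0 and 0.5 this is:

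- 0.85 × 0.36 + 0.1275 × 1.00 = 0.4335
- 0.85 × 0.36 + 0.1275 × 0.25 = 0.3379

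The standard error is √((0.4335 + 0.3379)/28) = 0.166, and 0.425/0.166 = 2.56. Larger gains make the imputed zeros add more variance, so power depends on the gains and not only on their difference. Simulated power with 15% lost in each arm:

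| True gains | LOCF | Observed data |
|---|---|---|
| 1.0 v 0.5 | 71% | 80% |
| 0.8 v 0.3 | 75% | 80% |
| 0.5 v 0 | 79% | 80% |

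LOCF itself therefore costs about 1 to 9 percentage points.

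**Week 8, unequal dropout, equal true gain g.** The bias is −(d_AT − d_BI) × g. For 25% v 5% and g = 0.5 it is −0.20 × 0.5 = −0.10.

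| Dropout AT v BI | Gain | Bias | Type I error |
|---|---|---|---|
| 18% v 12% | 0.5 to 0.8 | −0.03 to −0.05 | 5.3% to 5.9% |
| 20% v 10% | 0.5 to 0.8 | −0.05 to −0.08 | about 6% to 8% |
| 25% v 5% | 0.5 | −0.10 | 10% |
| 25% v 5% | 0.8 | −0.16 | 16% |
| 25% v 5% | 1.0 | −0.20 | 21% |

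Observed data give about 5% at the 25% v 5% split. With 15% lost in each arm, LOCF also gives about 5%.

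**Follow-up, share d carried from week 8.** The reported loss is (1 − d) × the completers' loss.

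- If a gain of 0.6 wanes to 0.30 and 15% are carried forward, the reported gain is 0.85 × 0.30 + 0.15 × 0.60 = 0.345. The reported loss is 0.255 instead of 0.30, so 15% of it is hidden.
- For a true loss of 0.5, the reported loss is 0.475 at d = 5%, 0.425 at 15% and 0.375 at 25%.
- If completers keep a gain of 0.5 and the missing 15% relapse fully, the true mean loss is 0.15 × 0.5 = 0.075. LOCF reports 0.

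**The case against.** **Equal dropout is also plausible.** Both arms receive 12 hours of contact, missed sessions are rescheduled and help with transport is available. At 18% v 12% the type I error is hardly raised. This stands: 25% v 5% is an illustration of a large imbalance, not a forecast.

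**Dropouts may gain less than completers.** The bias is the dropout gap times what the dropouts would truly have gained. If people who abandon the programme gain little, zero is closer to the truth, and a missing-at-random model would err the other way. This also stands. It is the reason for a sensitivity analysis, but it does not justify fixing the value at exactly zero.

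**The 15% limit bounds the rule.** It does not cure the problem. LOCF applies below the limit, the limit equals the loss that the plan expects, and nothing is stated for missingness above it.

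**Stronger readings that the documents do not support:**

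- A reader might infer that the plan guarantees a finding of maintained gains. Zero relapse is forced only on patients missing at follow-up. In the waning example the other 85% still show it, and the error is 0.045 points, under a tenth of the 0.5-point threshold.
- A reader might compare LOCF power with the 86% that 28 per arm would give without any dropout. No analysis recovers that figure once 15% are lost. The fair comparator is 80%.
- A reader might infer that the standard errors must be wrong because imputed values count as observed. In the week-8 comparison they are not: the empirical SD of the LOCF difference and its mean model standard error are 0.166 and 0.166 at equal dropout (gain 0.8), and 0.165 and 0.164 at 25% v 5%. The fault shown is bias.

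**Conclusion.** The point holds as a weakness that should be fixed; it does not invalidate the trial. That LOCF sets week-8 change to zero for early dropouts and relapse to zero for later ones follows directly from the stated rule and the visit schedule, without further assumption.

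The size is moderate at the planned 15% loss. A true difference of 0.5 becomes 0.425, power falls by about 1 to 9 points, and about 15% of a true relapse is hidden, or more if dropouts relapse more than completers. Type I error is close to nominal when dropout is nearly balanced and rises to 10% to 21% only under a strong imbalance. These figures rest on assumed gains, assumed splits and equal benefit in dropouts and completers. Both the shrinkage and the follow-up bias favour conclusions that the article anticipates or sets out to test: similarity and maintenance.

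**What to change.** Before outcomes are analysed, replace LOCF as the primary method with a likelihood-based mixed model for repeated measures that uses every observed ACQ value from all randomised patients. Multiple imputation would also serve. Add a sensitivity analysis for informative dropout, for example a delta-adjusted one, at both week 8 and follow-up. It is needed because the primary model relies on missing at random and would also miss a relapse confined to patients who leave. Keep LOCF at most as a further sensitivity analysis. Remove the 15% clause, or state what is done above it.

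The cost is revised analysis wording and software with a mixed-model or imputation routine. No new data or visits are needed. The change is still possible: the article reports recruitment and data collection as ongoing, with 52 participants recruited by October 2025. Made after the outcomes are seen, it would look data-driven.

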### Interventions

#### Asthma Education Program for Both Groups

All people in both groups will participate in a brief asthma education program of 90 minutes. The educational program will be conducted in a class through group discussions and video presentations. Educational topics will include asthma pathophysiology, medication and peak flowmeter use, self-monitoring of symptoms, environmental hygiene [1,26], and physical activity recommendations and benefits [17].

#### AT Group

Patients will undergo aerobic physical training on a treadmill twice weekly for 16 sessions, totaling 8 weeks of intervention. Each AT session will last 45 minutes, divided into 5 minutes of warm-up, 35 minutes of aerobic exercise, and 5 minutes of cool-down (2 sessions per week, 45 minutes each). The intensity will be based on the heart rate (HR) corresponding to one third of the difference between the anaerobic threshold and the respiratory compensation point (RCP), and is determined by CPET [27]. After 2 weeks of adaptation, the exercise intensity will be increased to two-thirds of the difference between anaerobic threshold and RCP, obtained via the CPET. If a patient proves capable of sustaining the new training intensity uninterruptedly for 2 consecutive sessions, without presenting respiratory symptoms, the exercise intensity will be increased by 5% of the HR up to a maximum of 85% of the participant’s maximum HR [2,3]. Before and after each exercise session, patients will be asked to measure the peak expiratory flow, and if the value is less than 70% of the predicted value or if patients present important symptoms of asthma before or during training, they will be instructed to use 400 μg of salbutamol via aerosol prescribed by their physician [28].

#### BI Group

The BI will be based on social cognitive theory and the stages of behavior change to increase the practice of physical activity in people with asthma [12,29,30]. Strategies such as motivational interviews, feedback, and guidelines to overcome barriers will be used to make it easier for participants to reach their goals. Individuals will receive a commercially available smartwatch activity monitor (Mi Band 5; Xiaomi) with an alarm that vibrates when the recommended daily number of steps is reached and if the individual remains sedentary for 60 minutes [12]. The main objective of the BI for people with asthma will be to increase PADL at any intensity and reduce sedentary time. The program will be carried out in individual sessions once a week, lasting 90 minutes each, for 8 sessions. At the beginning of the protocol, a motivational interview will identify each participant’s behavioral stage for the practice of physical activity through an appropriate questionnaire [31]. In addition, the participants will be asked to complete a daily physical activity diary and sign a contract with their health care professional [12].

Data from each week will be reviewed at every session of the behavioral intervention. Each individual will receive advice based on the smartwatch data. Each session will address different topics related to the practice of physical activity and sedentary behavior. Individuals will be motivated and encouraged to make behavioral changes. In the last session, a final motivational interview will be carried out to identify the change in the patient’s behavioral stage, taking stock of the goals reached or not, the benefits acquired with the changes made, the strategies to overcome the most significant barriers, and the establishment of new long-term goals to stay physically active. The schedule and content of each session are detailed in Table 1, which is reproduced from Freitas et al [32]. The Freitas et al [32] protocol will be modified only by changing the activity smartwatch monitor (Mi Band 5; Xiaomi) during the intervention instead of the Fitbit device [32].

**Table 1 table1:** Description of the behavioral change intervention sessions.

Number of weeks	Topics covered
Week 1: lifestyle choices	Motivational interview to establish an educational diagnosis. Identify the behavior stage regarding physical activity. Raise awareness of physical activity benefits. Provide the Mi Band 5 and ask them to wear it for at least 3 d each week.
Week 2: why become physically active?	Raise awareness of the physical activity international recommendations. Deepen the knowledge about the physical activity benefits for patients with asthma. Review Fitbit Flex 2 data of the past week and set one smart weekly goal (number of steps). Establish the action planning (goal) and sign a contract. Evaluate the confidence of patients in achieving the goal (self-efficacy). Explain about the use of the workbook, diary, and vibration alert.
Week 3: sedentary behavior	Raise awareness of the risks of prolonged uninterrupted periods of sitting. Ask them to start monitoring their sitting time (diary in a workbook). Discuss strategies to stand up/break up the sedentary time, according to the Fitbit Flex 2 vibration function. Review achievement (using the diary and Fitbit Flex 2 data) of the current goal. Discuss progress of the current goal. Set one smart weekly goal (number of steps).
Week 4: dealing with barriers	Dealing with barriers (as part of action and coping planning). Brainstorm the main barriers and possible solutions or modifications. Discuss preferred activities. Invite participants to come up with ideas for walking (progression in duration or intensity). Congratulate patients on any success (positive reinforcement) and ask them to reflect on any difficulties. Review achievement (using the diary and Fitbit Flex 2 data) of the current goal. Progress the current smart goal (number of steps and sedentary behavior).
Week 5: self-control	Facilitate self-control (how to self-monitor the negative and positive behaviors regarding PA^a^). Identify the benefits acquired with the lifestyle change and reinforce the commitment to change. Invite participants to come up with ideas to break up the sedentary time. Review achievement (using the diary and Fitbit Flex 2 data) of the current goal. Progress current goals as able or required.
Week 6: setting an additional goal	Review the initial goal and discuss the progress of this goal (challenges). Evaluate the confidence about achieving the new goal (self-efficacy). Reinforce the health benefits of increased participation in PA and of breaking up sedentary time. Congratulate on any success and reflect on any difficulties. Review achievement (using the diary and Fitbit Flex 2 data) of the current goal. Set a new smart goal as able or required.
Week 7: being rewarded	Identify the behavior stage regarding physical activity. Discuss the change (or not) that was achieved, as well as the benefits acquired with the new lifestyle. Discuss positive reinforcement. Review achievement (using the diary and Fitbit Flex 2 data) of the current goal. Set a final goal (number of steps).
Week 8: goal balance	Final motivational interview (goal setting, benefits acquired, and strategies to overcome barriers). Reinforce the importance of following through with these changes. Establish a long-term goal to stay physically active.

^a^PA: physical activity.

### Participant Timeline

The schedule of enrollment, allocations, interventions, and assessments is outlined in Table 2. The recruitment of the study participants began in August 2022.

**Table 2 table2:** Schedule of enrollment, interventions, and assessments.

Study period			Enrollment (t1)		Allocation (0)		Baseline		After allocation (8 wk)		Follow-up (16 wk)
